### Primary Outcome Measures

The Quality of Upper Extremity Skills Test (QUEST) is a commonly used outcome measure that evaluates quality of dissociated movements, UE gross motor function, and object manipulation in children with CP. It consists of 36 tasks evaluated in 4 domains: dissociated movement, grasp, protective extension, and weight bearing. The tool has demonstrated excellent test-retest reliability [42], and through construct validity studies, has been demonstrated as a good measure of UE motor skill [43].

The following subtests of the Peabody Developmental Motor Scale, Second Edition (PDMS-2) will be used: (1) object manipulation (24-item subtest that measures a child's ability to manipulate balls); (2) grasping (a 26-item subtest that measures a child's ability to use his or her hands [44]); and (3) Visual-Motor Integration (VMI) subtest (a 72-item subtest that measures a child's ability to use visual perceptual skills). Both the PDMS-2 fine motor composite score and the VMI subtest score have shown high test-retest reliability and have good construct validity [45,46].

Immediately following the 16-week intervention, a semi-structured interview format will be used to ask parents about the 5 most important activities their child was trying or wanted to do, but was having difficulty performing and/or difficulty in retaining.

## Results

We will test the difference between the experimental and control groups on the QUEST and PDMS-2 outcome measures using analysis of covariance (ANCOVA); the dependent variable will be the post-intervention measurement of the outcome and the covariates will be the pre-intervention measurement and group membership as the between-subjects effect. Residual diagnostics will be carried out for the ANCOVA model and if their normality assumption fails to hold, appropriate transformations of the response, such as logarithmic, will be explored. Based on published data for the primary outcome measures (QUEST and PDMS-2) [37-41], a power analysis was conducted to determine the required sample size to test the difference between the experimental and control groups using the ANCOVA model. We selected the case (QUEST) which gave the largest sample size. Assuming a correlation of at least 0.6 between baseline and final outcome, then with a sample size of 128 and a standard deviation of 25 we will be adequately powered to detect a difference of 10 units with 80% power, and 5% alpha post intervention. We expect an attrition rate of 10% over the study period. Given this, we propose to recruit a sample of 140 children to participate in equal numbers to be randomized to each group. All calculations were made with PROC GLMPOWER of SAS version 9.3 (SAS Institute, Cary, NC).

Feasibility will be evaluated on the basis of the 2010 Thabane et al model [47] which evaluates 4 domains: process, resources, effectiveness, and human and data management. Process evaluates feasibility of key study processes, such as participant recruitment rates, dropout rates, eligibility criteria, and participant retention rates. Resources, such as time taken to complete study assessments and other resource problems, will be reported over the study period by the project site leads from each site and the data will be compiled.

The parents of the children and the therapist experiences with the interventions and tools will be explored using semi-structured interviews using the qualitative description approach. The following open-ended questions will be asked of the children's parents: (1) when you agreed to participate, how did you hope your child would benefit from the therapy program? (2) Were there things about the game (or exercise therapy program) for your child you liked and things you did not like? (3) What did you think about the computer games your child was asked to play? Did your child enjoy the games? Were there games which your child did not seem to enjoy? (4) Did you feel that this therapy program helped your child? (5) If you were provided with the right setting, would you want your child to continue with these exercises?

The following open-ended questions will be asked of each treating therapist who delivered the game-based therapy program: (1) compared to usual therapy exercises how easy or difficult was it to implement the game exercise program for the children? (2) What kind of difficulties did you face, if any, regarding the use of the motion mouse or other parts of the technology? (3) What qualities did the computer game based intervention possess, if any, that made it more engaging and fun for the children than the conventional protocol? (4) Why would you like to recommend this intervention and technology to your peers, colleagues, and patients? (5) Are there any thoughts, queries, or doubts regarding this treatment method that you would like to express or discuss with us?

The responses of the parents and therapists will be analyzed with content analysis methods using the descriptive as well as interpretative approaches [48,49]. The data collected during the semi-structured interviews will be in the local language. Responses will be transcribed and translated by authorized personnel to organize the data by labelling, structuring, and familiarizing processes. Each participant’s data will be reviewed and analyzed by 2 researchers. Their narrative summary will then be sent back to the parents and therapist for review and approval to ensure trustworthiness of the transcribed and summarized data. Direct quotes from parents’ and physiotherapists’ interviews will be used while writing the descriptive report to illustrate a range of issues faced during the study, behaviors, experiences, and opposing views of participants and strategies. These will be used to develop general statements and hypotheses, which can be tested in subsequent studies. A second order analysis will take place by creating a coding plan based on the research questions. Once the data is coded and sorted, these responses will be categorized to identify themes. The recurrent themes and response clusters are helpful to build event sequences.

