## Methods

### Study Setting

This randomized controlled, single-blind clinical trial with an active control arm will be conducted at the following 4 sites: (1) University of Manitoba and Rehabilitation Centre for Children at the Special Services for Children and Youth (SSCY) Centre (Drs [name], [name], [name], and [name], Winnipeg, Manitoba, Canada); (2) SDM College of Physiotherapy, Dharwad in collaboration with Usha's School for Exceptional Children, Hubli (Drs [name], [name], [name], and [name], Karnataka, India); (3) Christian Medical College (Drs [name], [name], and [name], Ludhiana, Punjab, India); and (4) Kasturba Medical College ([name], Mangalore, Karnataka, India).

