### Inclusion Criteria

Children diagnosed with CP (N=140) between the ages of 4 and 10 years old with moderate UE impairments and fine motor control abnormalities will be recruited. The following screening tools will be used: (1) Manual Ability Classification System (MACS), level 2 to 3 [38]; (2) Gross Motor Function Classification Scale (GMFCS), levels 2 to 4 [39]; (3) Ashworth scale of spasticity in wrist and fingers, level 0 to 1+ [40]; and (4) the pediatric version of the Mini-Mental State Examination assessment scale, level 17 and above. This will be used to the screen level of cognitive function. For each site, we will use a permuted block randomization scheme stratified by age and level of impairment as measured by the MACS and GMFCS [41].

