### Procedures and Interventions

Ethical approval was obtained from the health research ethics boards of each site. For each site a permuted block randomization scheme will be used and stratified by age where 4- to 6-year-olds will be one subgroup and 6- to10-year-olds will be the other subgroup. Each program will take 16 weeks, with 3 45-minute sessions per week. A workshop and uniform training program will be organized at SDM College of Physiotherapy, Dharwad, India for physiotherapists who will provide the assessment and the 2 intervention programs. This will be attended by [name] and [name] who will organize and coordinate the therapy program. The 2 intervention groups will be treated in all 4 locations limiting biases like contamination. The therapists conducting the assessments will be blinded to group assignment.

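### The ANCOVA leaves out the stratification factors (site, age and possibly MACS and GMFCS), so to the extent that these are prognostic its standard error is too large and precision is lost

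*Protocol article*

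**What the plan says.** All references are to the protocol article.

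- **Study Setting** names four sites, one in Canada and three in India.
- **Inclusion Criteria** gives the allocation scheme: "For each site, we will use a permuted block randomization scheme stratified by age and level of impairment as measured by the MACS and GMFCS". The eligible range is two MACS levels ("Manual Ability Classification System (MACS), level 2 to 3") and three GMFCS levels ("Gross Motor Function Classification Scale (GMFCS), levels 2 to 4").
- **Procedures and Interventions** describes the scheme again but names age as the only factor within site: "For each site a permuted block randomization scheme will be used and stratified by age where 4- to 6-year-olds will be one subgroup". Impairment is not mentioned there.
- **Results** sets out the ANCOVA for QUEST and PDMS-2. The post-intervention score is the response, and "the covariates will be the pre-intervention measurement and group membership as the between-subjects effect". No other section adds a term.
- **Results** also gives the sample size: 128 children, SD 25, a difference of 10 units, 80% power and 5% alpha. It rests on one prognostic input: "Assuming a correlation of at least 0.6 between baseline and final outcome".

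**The concern.** Stratified blocks force the arms to be similar on the stratification factors. If those factors predict the outcome, the treatment estimate then varies less over repeated randomisations than it would under simple randomisation. A model that omits them leaves their variance in the residual, so its standard error does not show that gain. The reported standard error then exceeds the true one, confidence intervals are too wide, and the test rejects less often than its nominal 5%.

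At stake is the precision that the stratification was meant to secure. The factors are known for every child before randomisation, so the loss is avoidable.

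**Working it through.** **Inputs from the article.** Analysed N = 128, SD 25, correlation 0.6, difference 10, alpha 5% (taken as two-sided), four sites, two age groups, two MACS levels, three GMFCS levels.

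**Assumptions, not in the article.** First, the share R² of the baseline-adjusted residual variance that the factors explain, taken from 0 to 0.30. Second, a block size of 4. The simulation also lets the factors contribute equally and independently of the baseline score.

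**1. The article's own figure.** Residual SD after baseline adjustment = 25 × √(1 − 0.6²) = 20. Standard error of the group difference = 20 × √(4/128) = 3.54. A noncentral t with 128 − 3 = 125 df gives power 80.1%. The stated 128 therefore reproduces with baseline as the only covariate. A one-sided test would need 100 and no baseline adjustment 198, so neither fits.

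**2. The model with the factors added.** Residual SD becomes 20 × √(1 − R²). Main effects use 3 (site) + 1 (age) + 1 (MACS) + 2 (GMFCS) = 7 df. By noncentral t:

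| R² | Residual SD | Power at N = 128 | N for 80% power |
|---|---|---|---|
| 0 | 20.0 | 80.1% | 128 |
| 0.05 | 19.5 | 82.1% | 122 |
| 0.10 | 19.0 | 84.1% | 116 |
| 0.20 | 17.9 | 88.0% | 104 |
| 0.30 | 16.7 | 91.8% | 92 |

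Subtracting 80.1% from these powers overstates the gain. Under stratified allocation the unadjusted estimate also varies less, so the unadjusted model's own power rises a little. Simulation allows for this.

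**3. Simulation, N = 128, 6,000 runs per setting.** The true SE is the standard deviation of the unadjusted estimate over runs. Type I error is that of the unadjusted model.

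*Site × age × MACS × GMFCS (Inclusion Criteria)*

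| R² | Reported SE | True SE | Type I error | Power unadjusted → adjusted |
|---|---|---|---|---|
| 0 | 3.54–3.55 | 3.52–3.55 | 4.6% | 79.9% → 79.3% |
| 0.10 | 3.55 | 3.41–3.47 | 4.5% | 80.1% → 82.9% |
| 0.20 | 3.55 | 3.28–3.31 | 3.4% | 81.6% → 87.5% |
| 0.30 | 3.55 | 3.15–3.22 | 2.9% | 82.3% → 91.5% |

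*Site × age only (Procedures and Interventions)*

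| R² | Reported SE | True SE | Type I error | Power unadjusted → adjusted |
|---|---|---|---|---|
| 0 | 3.54 | 3.51–3.52 | 4.8% | 79.6% → 79.4% |
| 0.10 | 3.54 | 3.40–3.43 | 4.2% | 80.9% → 83.8% |
| 0.20 | 3.54–3.55 | 3.17–3.18 | 3.1% | 82.6% → 88.1% |
| 0.30 | 3.55 | 3.00–3.03 | 2.1% | 84.2% → 91.7% |

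The simulated gain is 82.9 − 80.1 = 2.8 or 83.8 − 80.9 = 2.9 points at R² = 0.10, and 87.5 − 81.6 = 5.9 or 88.1 − 82.6 = 5.5 points at 0.20. At R² = 0.05 a simulated gain of 1 to 2 points agrees with the 2.0 points from step 2.

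**4. Number of cells.** Crossing every level in Inclusion Criteria gives 4 × 2 × 2 × 3 = 48 cells. With 140 children that is 140/48 ≈ 2.9 per cell. Many blocks would stay incomplete, which is why the gap between reported and true SE is smaller under this scheme than under site × age.

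**The case against.** The strongest counter-argument is that nothing invalid follows. This stands. A reader might infer from the mismatch that the treatment estimate is biased, that false positives are inflated, or that the trial is underpowered. The documents support none of these. Randomisation protects the estimate, the error in the test runs in the conservative direction, and 128 was derived for the very model that is stated.

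The second is that the loss is conditional. This also stands. A reader might conclude that the standard errors are simply wrong, but that holds only if the factors predict the outcome beyond the baseline score. The article gives no figure for this. The model already adjusts for the baseline of the same measure, and part of what MACS predicts would plausibly be captured there. At a share of 0% nothing is lost.

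The third is that the list of stratification factors is itself unsettled, because the two descriptions differ on impairment. This stands for the covariate list but not against the principle, since the effect appears under either scheme.

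The last is that an article condenses, and further covariates may be set in an analysis plan that is not shown. This carries less weight. The article does more than announce an ANCOVA: it lists the terms, and its sample size reproduces with those terms alone.

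**Conclusion.** The point holds in conditional form. The stated ANCOVA does not reflect the randomisation. If the stratification factors explain 10% of the baseline-adjusted residual variance, the reported SE of 3.55 stands against a true value of about 3.4. At 20% the true value is about 3.3 under the full scheme or 3.2 under site × age. That makes the reported SE too large by about 7% (3.55/3.31) to 12% (3.55/3.17). These shares and the block size are assumptions, and the documents do not show which share applies.

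The planned 80% power at N = 128 is met by the model as written, so the sample size need not change on this account. The margin is thin, however: 140 less 10% attrition is 126 children, for whom the same calculation gives 79.5%. This is a worthwhile improvement to the analysis and does not put the trial's conclusions in doubt.

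**What to change.** 1. Reconcile Inclusion Criteria with Procedures and Interventions on whether MACS and GMFCS are stratification factors.
2. Restate the model for QUEST and PDMS-2 as: post score = group + baseline score + site (fixed, 4 levels) + age + MACS level + GMFCS level. Use main effects only, because a term for each crossed stratum would mean up to 48 cells for 140 children.
3. If impairment proves not to be a stratification factor, site and age are the required terms (3 + 1 = 4 df). MACS and GMFCS can stay as pre-specified baseline covariates.

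The cost is one sentence in the analysis section, fixed before unblinding, and at most 7 of 125 residual degrees of freedom. No new data are needed, since MACS and GMFCS are already recorded at screening. If the factors turn out not to be prognostic, power stays at about 80%.

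### Recruiting 140 with 10% attrition leaves 126 evaluable children, not the 128 used for power; the effect on power is negligible, but the stated figures should be made to agree

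*Protocol article*

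**What the plan says.** The sample-size paragraph stands in the Results section of the protocol article. The analysis is an ANCOVA in which "the dependent variable will be the post-intervention measurement of the outcome and the covariates will be the pre-intervention measurement", with group as the between-subjects effect.

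The inputs to the power calculation are:
- Correlation: "Assuming a correlation of at least 0.6 between baseline and final outcome".
- Size and spread: "with a sample size of 128 and a standard deviation of 25".
- Target: "to detect a difference of 10 units with 80% power, and 5% alpha post intervention".

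The attrition allowance follows directly: "We expect an attrition rate of 10% over the study period". The next sentence presents the recruitment target as the result of that expectation: "we propose to recruit a sample of 140 children to participate in equal numbers to be randomized to each group".

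The total of 140 appears again under Inclusion Criteria, and 70 per arm appears under both the Control Group and the Experimental Group Intervention. The article attributes all calculations to SAS PROC GLMPOWER. It gives no formula for the attrition allowance and no expected number of evaluable children.

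**The concern.** Three linked figures stand next to each other: 128 analysed, 10% lost, 140 recruited. The third is offered as what the first two imply, and it is not. Other places in the article repeat 140 and 70 per arm, so nothing elsewhere reconciles them.

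What is at stake is the consistency of the sample-size justification more than the power itself. Dropout and retention are among the feasibility measures named in the Results section, so a reader will compare observed losses with the planned allowance. As written, the article implies that 14 losses can be absorbed without going below 128, when only 12 can.

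**Working it through.** **Inputs (protocol article, Results).** Standard deviation 25; baseline-to-final correlation 0.6, the lowest value the article allows; difference 10; alpha 5%; power 80%; ANCOVA with the baseline value as covariate; 128 for power; attrition 10%; 140 recruited, 1:1. One assumption is added: the test is two-sided. The article does not say so, but the two-sided test reproduces its 128, while a one-sided 5% test needs only about 100.

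**Step 1: reproduce the plan's 128.**
- Residual SD = 25 × √(1 − 0.6²) = 25 × 0.8 = 20.
- Noncentrality = difference / (residual SD × √(4/N)), with N − 3 degrees of freedom (two groups, one covariate).
- At N = 128: 10 / (20 × √(4/128)) = 10 / 3.536 = 2.828. Noncentral t power = 80.1%.
- At N = 127, power = 79.8%.

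So 128 is the smallest total that reaches 80%, and the plan's figure is reproduced.

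**Step 2: apply the attrition.**
- Evaluable from 140 at 10% loss: 140 × 0.90 = 126, or 63 per arm. This is 2 short of 128.
- Recruitment needed to keep 128: 128 / 0.90 = 142.2, so 143, or 144 for equal arms.
- Multiplying in place of dividing: 128 × 1.10 = 140.8, so 141. Rounding this down would give 140, but the article does not say how 140 was obtained.
- Attrition that 140 can bear while keeping 128: (140 − 128) / 140 = 12/140 = 8.57%.

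**Step 3: the effect on power.**

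| Evaluable N | Noncentrality | Power, noncentral t | Difference detectable at 80% power |
|---|---|---|---|
| 128 | 2.828 | 80.1% | 9.98 units |
| 126 | 10 / (20 × √(4/126)) = 2.806 | 79.5% | 10.06 units |

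The loss is 0.6 percentage points.

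**Step 4: sensitivity at N = 126.**
- Correlation 0.60: 79.5%. Correlation 0.61: 80.3%. The 80% mark is crossed at about 0.607.
- With correlation 0.60, an SD of about 24.85 in place of 25 also restores 80%.
- By the normal approximation, power at 126 is 80.1%.

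**The case against.** The strongest case against raising this is that it is only rounding. Power is stated as a whole percentage, and 79.5% rounds to 80%. The correlation is a minimum, so power at 126 falls below 80% only for correlations between 0.600 and about 0.607. The SD of 25, the difference of 10 and the 10% attrition are round planning values, and 8.6% could loosely be called 10%. The detectable difference is 10 units to the nearest unit either way. Recruitment, allocation and analysis would not change.

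Nearly all of this stands as to size, and it defeats a stronger reading that a reader might infer: that the trial is underpowered, or that the plan has no margin for the two missing children. The documents support neither. The minimum on the correlation is itself a margin, and the shortfall is smaller than the precision of the inputs.

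Two parts do not remove the point. The normal approximation gives 80.1% at 126, but it is not the plan's method: it would have returned 63 per arm, or 126 in total, where the article reports 128 from PROC GLMPOWER. And rounding the power does not make 140, 10% and 128 agree. The article derives 140 from a 10% loss, and a 10% loss from 140 does not leave 128.

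Nor does it help that a journal article condenses a fuller protocol. Nothing is said to be missing here; the figures that are printed disagree.

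**Conclusion.** The attrition allowance is miscalculated by two evaluable children. The slip in the counts is certain, since it follows from three stated figures alone. The effect on power is negligible: a loss of 0.6 points that leaves power at about 80%. That size rests on the two-sided test, a correlation exactly at the stated minimum, and a noncentral t calculation with one covariate. This is a low-severity correction of stated figures. It does not bear on the validity of the trial and is no reason to enrol more children.

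**What to change.** Keep the target of 140 and reword the attrition sentence in the Results section in one of two ways:

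1. Keep 10% attrition, and state that 126 evaluable children are expected, giving about 79.5% power for a 10-unit difference at correlation 0.6 (80% or more if the correlation is about 0.607 or higher).
2. Keep 128 as the evaluable number, and state that 140 tolerates 12 losses, about 8.6%.

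A target of 144 would be the arithmetically consistent one for 10% attrition with equal arms, but the power at stake does not call for it. In either version it would help to add that the 5% alpha is two-sided, if that is what was used.

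The cost is one sentence. The only downside is a very slightly less favourable stated figure; the conduct of the trial does not change.

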### Study Design

This study will evaluate the feasibility of the procedures such as recruitment, intervention delivery, participant retention, and measurement tools. Semi-structured interviews will be conducted with the parents of the children and with the treating therapists. The broad research questions are: “what were the experiences of the study participants with the game-based and current therapy programs, and on what context were the experiences based?” The qualitative findings of participant's and therapists' experiences will help to identify (1) perceived exercise benefits; (2) difficulties with the exercises and using the technologies; (3) engagement and motivational value of the computer games; (4) personal and environmental factors that influenced doing the exercises; and (5) recommendations and modifications for improving the exercise programs.

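### Two of the five listed therapist interview questions, on recommendation and on engagement, are worded towards a favourable answer and should be made neutral

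*Protocol article*

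**What the plan says.** The Study Design section of the protocol article plans semi-structured interviews with parents and treating therapists. The broad research question begins "what were the experiences of the study participants with the game-based and current therapy programs". Among the five things the qualitative findings are meant to identify, the third is how far the games engage and motivate the children. The Discussion repeats this target.

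The Results section lists the therapist questions, to be "asked of each treating therapist who delivered the game-based therapy program":

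- Question 1 (implementation): "compared to usual therapy exercises how easy or difficult was it to implement the game exercise program for the children"
- Question 2 (technology): "What kind of difficulties did you face, if any, regarding the use of the motion mouse or other parts of the technology"
- Question 3 (engagement): "What qualities did the computer game based intervention possess, if any, that made it more engaging and fun for the children than the conventional protocol"
- Question 4 (recommendation): "Why would you like to recommend this intervention and technology to your peers, colleagues, and patients"
- Question 5 (closing): "Are there any thoughts, queries, or doubts regarding this treatment method that you would like to express or discuss with us"

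The same section says that the answers will undergo content analysis. Two researchers review each participant's data, summaries go back to respondents for approval, and the coded themes feed general statements and hypotheses for later studies.

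**The concern.** An interview meant to learn whether therapists would adopt a technology should let them say no as easily as yes. Question 4 asks for the reasons behind a recommendation without first establishing that there is one. Question 3 collects the game's advantages over conventional therapy but has no partner that collects its disadvantages. Recommendation and engagement are the two topics on which a reader would most want a balanced account, and the Introduction states that the study team developed the platform, which makes neutral wording more important. At stake is the credibility of the qualitative findings on these two topics. No efficacy result is at stake.

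**Working it through.** No formula or figure applies, because the point concerns wording. The check is to read all five therapist questions for two properties: does the question assume its answer, and can it draw out an unfavourable view as directly as a favourable one?

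1. **Question 1 (implementation).** It assumes nothing and names both directions, ease and difficulty. Neutral.
2. **Question 2 (technology).** It asks for difficulties and is qualified by *if any*. It leans towards unfavourable experience.
3. **Question 3 (engagement).** The *if any* means that it does not assume an advantage, and a therapist can answer that there was none. The direction is still fixed: only qualities that made the game more engaging are requested. A therapist who found it less engaging for some children, or who saw conventional therapy do better, is not asked to say so.
4. **Question 4 (recommendation).** It assumes the answer. There is no *whether* and no *if any*, although questions 2 and 3 carry that qualifier. A therapist who would not recommend the platform must reject the premise before replying.
5. **Question 5 (closing).** It is open and expressly invites doubts. Neutral.

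The count is one presupposing question (question 4), one single-direction but qualified question (question 3), and three that are neutral or invite criticism (questions 1, 2 and 5): 1 + 1 + 3 = 5.

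The next step is to set this against the stated aims. Engagement is named as a target in both Study Design and the Discussion, and question 3 is the only listed therapist question on it. Recommendation is raised only in question 4. On each topic, then, the tilted question is the only dedicated therapist question.

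The last step is to ask whether the planned analysis can correct the tilt. Review by two researchers and return of summaries check that what was said is recorded faithfully. They cannot supply answers to a question that was not put.

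**The case against.** The strongest reply is that the set as a whole is reasonably balanced. Three of the five therapist questions are neutral or invite criticism. Question 3 carries its qualifier. Parents are a second source: they are asked what they disliked as well as what they liked, and whether there were games the child did not enjoy. The interviews are semi-structured, so a therapist may answer question 4 by declining to recommend. The Results section plans to report opposing views and treats the findings as generating hypotheses. Feasibility is judged through recruitment, dropout, retention, time and resources, and does not depend on question 4.

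Most of this stands, and it limits the point. It does not remove it: general openness elsewhere in the interview does not make a leading question neutral, and the parents' answers do not replace the therapists' own view of recommendation or comparative engagement.

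Four stronger readings are tempting, and the article does not support them:

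- *The favourable conclusion is built into the interview.* Questions 1, 2 and 5 contradict this.
- *Two of five questions (40%) presuppose a favourable view.* Only question 4 presupposes anything. Question 3 has a different and milder defect.
- *Only one arm's therapists are heard.* The listed questions do go to those who delivered the game. However, Procedures and Interventions describes training physiotherapists to provide both programmes and does not say that therapists are split by arm. Questions 1 and 3 also expect respondents to know usual therapy.
- *Control parents are asked about games their child never played.* The article does not say that this item goes to control parents. Another parent question is worded for either programme, and a semi-structured interview can skip an item that does not apply.

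**Conclusion.** The point holds in a narrow form. Question 4 presupposes a recommendation, and question 3 asks about engagement in one direction only. Therapist answers on these two topics will be tilted towards the platform if the questions are put as printed. How far the resulting themes would shift cannot be estimated from the article.

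This rests on two assumptions: that the printed questions are the ones to be asked, and that no neutral probe in a fuller interview guide, which is not shown, offsets them. The matter is minor. It concerns a descriptive, hypothesis-generating component and leaves the QUEST and PDMS-2 comparisons untouched.

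**What to change.** Reword two questions in the therapist guide:

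- Question 4: *Would you, or would you not, recommend this programme, and why?*
- Question 3: *How engaging was each programme for the children, and what made the game more or less so than the conventional protocol?*

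Questions 1, 2 and 5 can stay as they are. The cost is a revised interview guide notified to the ethics boards. The number of interviews, the trial design and the quantitative analysis do not change.
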